## Abstract

**Background:**

Transcranial direct current stimulation (tDCS) is a technique that can noninvasively modulate neural states in a targeted brain region. As cerebellar activity levels are associated with upper limb motor improvement after stroke, the cerebellum is a plausible target of tDCS. However, the effect of tDCS remains unclear. Here, we designed a pilot study to assess: (1) the feasibility of a study that aims to examine the effects of cerebellar tDCS combined with an intensive rehabilitation approach based on the concept of constraint-induced movement therapy (CIMT) and (2) the preliminary outcome of the combined approach on upper limb motor function in patients with stroke in the chronic stage.

**Methods:**

This pilot study has a double-blind randomized controlled design. Twenty-four chronic stroke patients with mild to moderate levels of upper limb motor impairment will be randomly assigned to an active or sham tDCS group. The participants will receive 20 min of active or sham tDCS to the contralesional cerebellum at the commencement of 4 h of daily intensive training, repeatedly for 5 days per week for 2 weeks. The primary outcomes are recruitment, enrollment, protocol adherence, and retention rates and measures to evaluate the feasibility of the study. The secondary outcome is upper limb motor function which will be evaluated using the Action Research Arm Test, Fugl-Meyer Assessment, for the upper extremity and the Motor Activity Log. Additionally, neurophysiological and neuroanatomical assessments of the cerebellum will be performed using transcranial magnetic stimulation and magnetic resonance imaging. These assessments will be conducted before, at the middle, and after the 2-week intervention, and finally, 1 month after the intervention. Any adverse events that occur during the study will be recorded.

**Discussion:**

Cerebellar tDCS combined with intensive upper limb training may increase the gains of motor improvement when compared to the sham condition. The present study should provide valuable evidence regarding the feasibility of the design and the efficacy of cerebellar tDCS for upper limb motor function in patients with stroke before a future large trial is conducted.

**Trial registration:**

This study has been registered at the Japan Registry of Clinical Trials (jRCTs042200078). Registered 17 December 2020

## Background

Functional recovery of the upper limb is one of the primary goals of those who suffer a stroke. In the last two decades, transcranial direct current stimulation (tDCS) has been widely investigated as a noninvasive brain stimulation technique that can enhance rehabilitation outcomes along with the modulation of brain activity [1]. Several studies using functional magnetic resonance imaging (MRI) [2, 3] or transcranial magnetic stimulation (TMS) [4–7] have shown that tDCS has the potential to enhance neural plasticity. Many studies have attempted to facilitate motor recovery after stroke by applying tDCS to the primary motor cortex (M1) [8, 9]. However, there is no consensus among systematic reviews regarding the effectiveness of tDCS for motor function after stroke. For instance, a recent review suggested that tDCS has significant effects on upper limb motor function in patients with stroke in the chronic stage [8]. However, a network meta-analysis, which synthesized the effects of multiple interventions (i.e., anodal, cathodal, and bilateral tDCS), showed that only cathodal tDCS had moderate effects on levels of activities of daily living (ADL), while no significant effects on the upper limb motor function were noted [9].

Recently, the neuromodulation of the cerebellum has gained increased attention. The cerebellum has multiple connections with motor and non-motor cerebral cortices and plays an important role as a hub of the brain network [10, 11]. Among a wide range of cerebellar functions, its contribution to the motor domain, especially the learning processes, would be essential to patients after stroke [12, 13]. Several imaging studies have suggested that increased cerebellar activity is associated with motor function improvement after stroke [14–18]. On the other hand, cerebellar inactivity such as crossed cerebellar diaschisis, which is caused by decreased blood flow and metabolism in the cerebellar hemisphere due to decreased neural inputs after stroke, is associated with functional impairments [19, 20]. Furthermore, it has been reported that functional connectivity between M1 and the cerebellum [11, 21] and the structural integrity of the cortico-cerebellar tract [17, 18] seem to be related to motor recovery after stroke. These findings demonstrate the importance of the cerebellum and its functional connectivity to motor cortices, indicating that upregulating cerebellar neural activity would be beneficial for motor recovery after stroke [22, 23]. Supporting this hypothesis, animal studies reported that, compared to sham stimulation, applying deep brain stimulation to the cerebellum in stroke-model rats resulted in superior motor improvement in association with neuroplastic changes in the area around a lesion [24–26]. Considering these findings, the cerebellum is a promising target for neuromodulation to facilitate improvements in motor function after stroke.

In stroke rehabilitation, intensive task-oriented training is crucial for facilitating motor recovery. Constraint-induced movement therapy (CIMT) is a well-known approach for improving upper limb motor function after stroke. The key element in CIMT is that it encourages the use of the affected arm through intensive functionally oriented tasks [27, 28]. Although it is generally accepted that neural and functional recovery reaches a plateau around 6 months after stroke onset [29], reviews have shown the effectiveness of CIMT in post-stroke survivors in the chronic stage [30, 31]. In addition, several stroke guidelines highly recommend CIMT as a beneficial approach for improving upper limb motor function and activity especially in the chronic stage [32, 33]. Furthermore, studies reported that CIMT combined with tDCS [34, 35] or combined with tDCS and the peripheral electrical stimulation [36] of motor-related cerebral regions induced greater effects on upper limb motor function compared to CIMT alone.

In view of these, we hypothesized that a combination of cerebellar tDCS and intensive movement therapy would further facilitate the improvement of motor function in stroke patients in the chronic stage. To clarify this hypothesis, we designed the present study to assess (1) the feasibility of a study that will examine the effects of cerebellar tDCS combined with intensive upper limb training and (2) the preliminary effects of this combined approach on upper limb motor function. The present study details a pilot trial that will be conducted before a large-scale randomized controlled trial.

## Methods/design

### Study design

This study is a double-blind randomized controlled pilot trial and was designed according to the Consolidated Standards of Reporting Trials (CONSORT) extension to pilot trials [37]. The study flowchart is shown in Fig. 1. Twenty-four stroke patients will be enrolled and randomly allocated to an active or sham tDCS group. This study will be conducted at Fujita Health University Hospital, Aichi, Japan. All participants will provide written informed consent before participation according to the Declaration of Helsinki of 1964, as revised in 2013. This study has been approved by the Certified Review Board at Fujita Health University (approval No. CR21-029) and registered at the Japan Registry of Clinical Trials (jRCTs042200078).

**Fig. 1 Fig1:**
[figure not shown]
Study flowchart

### Participants

The inclusion criteria are as follows: (1) age 40–79 years, (2) first-ever unilateral supratentorial ischemic or hemorrhagic stroke, (3) time exceeding 6 months after stroke onset, (4) mild to moderate upper limb hemiparesis [able to score ≥ 1 point on at least one item either in the grasp, grip, or pinch subscale with assessing all items of the ARAT; total score of 10–51], and (5) independent walking ability [score of ≥ 6 on the Functional Independence Measure (FIM) for a walk]. The exclusion criteria are as follows: (1) unstable physical condition, (2) inability to communicate due to severe language impairment, (3) neurological disorders other than stroke, (4) facial sensory deficits, (5) inability to perform training because of psychological disorders or cognitive dysfunction, (6) cognitive impairments [Mini-Mental State Examination (MMSE) < 24] [38, 39], (7) inability to perform training because of musculoskeletal disorders, (8) botulinum toxin injections into the arm within the last 6 months, and (9) any contraindications to tDCS, TMS, and MRI such as a history of epilepsy, metallic implants, cardiac pacemaker, drug or alcohol abuse, or pregnancy.

### Recruitment

Potential participants will be identified from the outpatient clinic of the University Hospital and the local community. The advertisement for the study is open to the public via our department website to allow patients in the local community to access relevant information. Individuals who are interested in this study will be required to make an appointment for screening. The eligibility of potential participants will first be carefully assessed by a physician. They will then be screened for motor and cognitive functions using the ARAT and MMSE by a trained occupational therapist. Written informed consent will be obtained from those who fulfill the criteria and are willing to take part in this study.

### Randomization

Participants will be stratified according to age and ARAT score and randomly allocated to either the active tDCS or sham tDCS group using a computer-generated, permuted block randomization method with permuted block sizes of 2 and 4. The random allocation will be conducted using the Research Electronic Data Capture (REDCap) tools [40] by independent researchers who will not be involved in any intervention and assessments.

### Interventions

A time schedule of this study is shown in Fig. 2A. The participants will be admitted to Fujita Health University Hospital. The participants will receive individual therapy of intensive upper limb training for 4 h per day (2 h per half-day) and engage in self-training for 2 h per day (1 h per half-day) and receive cerebellar tDCS (active or sham) for 20 min at the beginning of the intensive training (Fig. 2B), considering that the effects of tDCS on the neural excitability of a targeted brain region last for 30–120 min [2, 5–7]. This will be repeated for 5 consecutive days per week for 2 weeks (i.e., 10 days of intervention). During the intervention period, botulinum toxin injections and any changes of medications that could affect spasticity will not be allowed.

**Fig. 2 Fig2:**
[figure not shown]
Study protocol. **A** Schedule of the study. The intensive upper limb training and tDCS interventions will be repeated for 5 consecutive days per week for 2 weeks (i.e., 10 days of intervention). During the middle 2 days, the participants will receive only the upper-limb intensive training and self-training. Assessments will be conducted prior to the intervention (t_0_, baseline), at the middle of the intervention (t_1_, middle), immediately after the intervention (t_2_, post), and 1 month after the intervention (t_3_, follow-up). **B** Training schedule per day. Participants will undergo intensive upper limb training for 4 h per day (2 h per half-day) and receive cerebellar tDCS (active or sham) for 20 min during the beginning of the training. They also engage in self-training for 2 h per day (1 h per half-day). **C** Time course of active (upper panel) and sham (bottom panel) tDCS conditions

#### tDCS

The stimulation will be delivered using DC STIMULATOR PLUS (NeuroConn, GmbH, Ilmenau, Germany). The anode (5 × 5 cm) will be placed on the cerebellar hemisphere on the contralesional side. Specifically, lobule VI, one of the subregions contributing to motor control of the upper limb [41], will be a focal target of the stimulation. Conventionally, the anode is placed at the fixed position 3 cm lateral to the inion [42]; however, in the present study, the optimal location for targeting the lobule VI will be determined for each individual using computational simulation (see Computational modeling subsection). The cathode (5 × 5 cm) will be placed on the cheek on the contralesional side.

The detailed time course of active and sham tDCS is shown in Fig. 2C. The “study mode” of the NeuroConn stimulator will be used to successfully implement double-blinding using 5-digit codes that activate the active or sham stimulation. Only the independent researchers that conduct the random allocation can access the code list. The experimenter will remain blinded to the information regarding which code belongs to the active or sham stimulation. In the active tDCS group, 1 mA constant current will be delivered for 20 min, whereas in the sham tDCS group, 1 mA constant current will be delivered for 40 s to induce similar scalp sensations. In both groups, the current will be ramped up to 1 mA and ramped down over 15 s at the start and end of the stimulation [43]. During the sham tDCS condition, only a weak current of 110 μA will be delivered every 550 ms after the ramped-down periods to test the electrode impedance. Only the impedance level and stimulation duration will be displayed in both conditions, which facilitates the blinding of the experimenter. The sham procedure is commonly used in tDCS research and at least 30-s active stimulation with a slow ramp up and down are recommended for effective blinding during sham sessions [44]. The participants will not be given any information about stimulation parameters.

#### Intensive upper limb training

Intensive upper limb training based on the concept of CIMT will be provided by five trained occupational therapists who will be blinded to the intervention allocation. One of the occupational therapists with 3 years of CIMT experience trains the others and the training approach will be standardized among them. Each participant will be provided with the intensive upper limb training one-on-one by total 3–4 therapists throughout the intervention period depending on their work shift. CIMT is a therapeutic package that consists of repetitive and task-oriented training, behavioral methods for transferring the use of the affected arm in life situations, and constraining the use of the less affected arm to achieve participants’ specific goals [45]. Since previous studies have reported that physical restraint has no significant effects on the outcome of CIMT [46, 47], no restraints will be applied to the unaffected arm of the participants in this study. Another difference compared to the original CIMT is with respect to the training hours per day, with 4 hours in this study compared to 6 hours in the original [27]. To accomplish sufficient training, participants will be encouraged to use their affected arm in activities of daily living. Additionally, the participants will engage in self-training programmed by the occupational therapists for 2 h per day (Fig. 2B).

At the beginning of the intensive training, specific activities which the participant will aim to be able to reacquire and perform using their affected arm in the ADL/instrumental ADL will be discussed and selected as goals between a therapist and participant. Furthermore, training programs (task-oriented training) specific to an individual participant will be determined by the occupational therapists, considering the goals and remaining function of the affected arm of each participant. For example, when a participant’s goal is to reacquire eating, task-oriented training would be moving blocks to several directions and heights and more practical training of picking up small objects and bringing them to the mouth using a utensil, etc. To provide consistent training among the therapists, they will discuss and share the training programs using videos and photos (types of objects, motion, etc.) throughout the intervention period, at least two times at the beginning and middle (after 1 week) of the intervention period. If necessary, functional electrical stimulation will be provided to enhance muscle contractions and perform functional tasks, but rehabilitative robots will not be allowed.

#### Computational modeling

Figure 3 shows the method that will be used to optimize the location of the tDCS montage at the individual level. First, the head model will be treated as a passive volume conductor constructed from 3D T1- and T2-weighted MRI of each participant before the experiment. The computational method has been reported in detail in a previous report [48, 49]. It involves using the scalar potential finite difference method with fast computational techniques to accelerate the computational assessment before the intervention [50, 51]. The computational model estimates the individualized electric field intensity and distribution on the cerebellar region by applying a bipolar montage throughout the electrodes (5 × 5 cm) with an injection current of 1 mA, as used in the experiment. The cathode will be fixed on the buccinator muscle on the cheek on the contralesional side to avoid high-electric currents flowing on the cerebrum. The anode will be placed on a grid (13 × 11, size of grid = 10 mm) centered on the inion to identify the position that generates the highest electric field strength (maximum and average values), with lobule VI as the target area. The optimal electrode location will be determined based on a reference landmark (10–20 system) and the Montreal Neurological Institute coordinates for confirmation.

**Fig. 3 Fig3:**
[figure not shown]
Computational method to determine the optimal individualized position of the tDCS montage. **A** Head model segmentation. The volume conductor of the head model of each participant will be constructed from the segmentation of MRI data. **B** Computational modeling of a representative example. The individualized electric field on the cerebellum using a bipolar montage (anode in yellow and cathode in blue) will be simulated. **C** Optimal montage position. The optimal location of the anode that maximizes the electric field strength (maximum and average) on the region of interest (lobule VI) is selected from a grid of 13 × 11 positions

### Outcomes

#### Feasibility

Referring to the previous recommendations [52, 53], we will evaluate the feasibility of this pilot study based on the following measures: (1) recruitment and enrollment rates: the proportion of participants who meet the eligibility criteria and provide consent after baseline screening (enrollment rate) and the mean number of participants enrolled in the study per month (recruitment rate); (2) adherence rate: the proportion of completed training hours including individual therapy and self-training of the scheduled hours, which will be used to assess the acceptability of the interventions; and (3) retention rate: the proportion of participants who complete the secondary outcome measurement (i.e., ARAT) from the baseline to follow-up assessments.

These measures will be used as the progression criteria to determine whether to proceed with a future main trial [54]. The criteria are as follows: (1) enrollment rate: more than 30% of screened patients consent to enroll [55]; (2) recruitment rate: more than 0.8 participants are enrolled per month [20% of total target recruitment (5 participants) are enrolled in 6 months]; (3) adherence rate: participants complete more than 90% of scheduled training hours (61 hours on average); and (4) retention rate: more than 80% of enrolled participants (20 participants) with all outcomes until follow-up [30, 56]. If at most three criteria are failed and the issues behind them are manageable, the main trial will proceed with some protocol modifications. If all the criteria are not satisfied, the main trial will not proceed [54, 57]. It should be noted that, although the criteria are determined based on the previous studies and our own experiences, we may need to flexibly reconsider the criterion for the recruitment rate in the case of the COVID-19 pandemic.

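### The 61-hour gloss on the adherence progression criterion does not follow from the training hours written in the text, and the scheduled total behind it is not stated

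*Protocol article*

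**What the plan says.** The abstract lists protocol adherence among the primary outcomes. Under Outcomes, Feasibility, the adherence rate is "the proportion of completed training hours including individual therapy and self-training of the scheduled hours". The matching progression criterion is "participants complete more than 90% of scheduled training hours (61 hours on average").

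The schedule is described in two places:

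- **Interventions section.** The therapy component is "individual therapy of intensive upper limb training for 4 h per day (2 h per half-day"). Separately, for self-directed practice, the same section has participants "engage in self-training for 2 h per day (1 h per half-day"). The number of days is given next: "This will be repeated for 5 consecutive days per week for 2 weeks (i.e., 10 days of intervention").
- **Fig. 2 legend.** It repeats the 10 days and adds: "During the middle 2 days, the participants will receive only the upper-limb intensive training and self-training". For the daily timetable it says "Participants will undergo intensive upper limb training for 4 h per day (2 h per half-day"), again with 2 h of self-training. It gives no separate hours for the middle 2 days.

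The total number of scheduled hours appears nowhere in the text. On the consequence of missing a criterion, the Feasibility section says: "If at most three criteria are failed and the issues behind them are manageable, the main trial will proceed with some protocol modifications". The main trial is ruled out only when all four criteria are missed.

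**The concern.** The criterion is stated twice in one line, once as a percentage and once in hours. The two should be the same threshold, and the hours should be obtainable from the schedule. With the daily load in the text they are not, whether the middle 2 days are left out or counted at the usual load.

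The adherence verdict may then depend on which expression is applied and which total is used as the denominator. If both stay open until the pilot is complete, they can be settled after the data are known, which a preset progression criterion is meant to prevent.

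**Working it through.** **Inputs**

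- Therapy 4 h per day and self-training 2 h per day (Interventions; Fig. 2 legend): 4 + 2 = 6 h per day. Both components count towards adherence (Feasibility).
- Days: 10 (Interventions), plus 2 middle days with training and self-training but no stimulation (Fig. 2 legend).
- Threshold: 90%, given as 61 h (Feasibility).

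**Formula:** threshold in hours = 0.90 × total scheduled hours.

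**Step 1. Try to reproduce 61 h from the hours in the text.**

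| Reading | Scheduled hours | 90% of total | 61 h as share of total |
|---|---|---|---|
| 10 days at 6 h | 60 | 54.0 | 61/60 = 101.7% |
| 12 days at 6 h | 72 | 64.8 | 61/72 = 84.7% |
| Therapy only, 10 days at 4 h | 40 | 36.0 | 152.5% |
| Therapy only, 12 days at 4 h | 48 | 43.2 | 127.1% |

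None gives 61. The therapy-only rows also conflict with the definition of adherence, which includes self-training.

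**Step 2. Work back from 61 h.** 61 / 0.90 = 67.8 h. Allowing for rounding to a whole hour, 60.5 / 0.90 = 67.2 h and 61.5 / 0.90 = 68.3 h. With 60 h on the 10 main days, each middle day would hold between (67.2 − 60)/2 = 3.6 h and (68.3 − 60)/2 = 4.2 h.

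**Step 3. Find a schedule that fits.** 10 × 6 h + 2 × 4 h = 68 h, and 0.90 × 68 = 61.2 h, which rounds to 61. The same total comes from therapy on 12 days with self-training on 10: 12 × 4 + 10 × 2 = 68 h. That second route conflicts with the Fig. 2 legend, which places self-training on the middle days too. The first route needs a shorter middle day, which the text does not mention. Taking 20 min of stimulation on each of 10 days out of 72 h leaves 68.67 h, and 90% is 61.8 h, which rounds to 62.

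**Step 4. Where the two expressions disagree.**

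- Total 60 h: a mean above 54 h and up to 60 h meets the percentage but misses 61 h. Full attendance would miss it.
- Total 72 h: a mean above 61 h and up to 64.8 h meets the hour figure but misses the percentage.
- Total 68 h: the thresholds are 61 h and 61.2 h, so disagreement is confined to 0.2 h.

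**The case against.** The strongest reply is that 61 h is probably right and its source is simply not visible here. Fig. 2A shows the study schedule and was not available for this review, so it may set out a middle day of about 4 h. The 68 h total then gives 61.2 h, and the percentage and the hours agree to rounding. The 72 h total is itself an inference, because it carries the 6 h load over to days whose hours the text does not list. The 60 h total is open to challenge as well: read with the Fig. 2 legend, the 10 days may count only the days that combine stimulation and training, with further training hours accruing on the middle days. Finally, adherence is defined as a proportion, so the percentage is naturally the operative rule and the hours only illustrate it.

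Much of this stands. A reader might infer that 61 h matches no schedule in the plan, that the criterion can never be met, or that the correct figure must be 54 h or 64.8 h. The documents support none of these. The first needs the middle-day hours, the second needs the Fig. 2 legend to be set aside, and the third excludes the 68 h case. A reader might also call this a go/no-go error, but up to three missed criteria still allow the main trial with modifications if the issues are manageable.

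The reply does not remove the point. The 68 h total is recovered from the very number being checked. It needs either a shorter middle day that the text does not mention or a middle day without self-training, which the legend contradicts. The Interventions section does not mention training on the middle days at all.

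**Conclusion.** The point holds as an unreconciled threshold, not as a proven arithmetic error. With the hours in the text, 90% is 54 h or 64.8 h. The stated 61 h is 7.0 h above the first (61 − 54) and 3.8 h below the second (64.8 − 61). It agrees with 90% only for a total of about 68 h, which the text does not give.

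The size of the problem depends on the intended total. At 68 h it is a missing denominator with almost no effect on the verdict. At 60 h or 72 h the percentage and the hour figure disagree over the ranges in step 4.

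The effect on progression is limited. Taken alone, a missed adherence criterion moves the outcome from proceeding as planned to proceeding with modifications. It contributes to a stop only if the other three criteria are missed as well. This assumes that meeting all four means proceeding unchanged, which the section implies but does not spell out.

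**What to change.** 1. Reconcile the Interventions section, the Fig. 2 legend and the adherence criterion on the number of training days and the hours on the middle 2 days. Which schedule is intended is for the sponsor to declare; this review does not presume it.
2. State the total scheduled training hours next to the definition of the adherence rate.
3. Restate the hour figure as 90% of that total. If the total proves to be 68 h, the present figure can stay as a rounded value once the total is given.
4. Say that the percentage of scheduled hours governs and that the hour figure is illustrative.

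The cost is at most one restated number, plus a wording reconciliation. If the text is only brought into line with the schedule already in use, trial conduct does not change. The correction should be made before adherence data are summarised.
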